### Safety monitoring

Possible adverse events (AEs) due to moxibustion include blisters, redness, itching, burns, and respiratory symptoms. All unexpected and unintended responses will be reported as AEs by the researcher at every visit, even if they are not necessarily related to moxibustion intervention. The AEs will be carefully recorded in the CRF by the corresponding research staff.

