**Methods/Design:**

This protocol is for a randomized controlled trial in which the assessor and statistician will be blinded. A total of 222 eligible patients with dysmenorrhea will be randomly assigned to three groups in a 1:1:1 ratio as treatment group A (treated before menstruation onset), treatment group B (treated at the onset of menstruation), or control group C (waiting list group). The participants assigned to the treatment groups will receive suspended moxibustion treatment at *Sanyinjiao* (SP6) and *Guanyuan* (CV4), while the waiting list group will not receive moxibustion treatment until the completion of the study. The trial period will consist of three baseline menstrual cycles, three menstrual cycles of treatment, and three menstrual cycles in the follow-up period. The primary outcome will be measured by changes in the Cox Menstrual Symptom Scale and the secondary outcomes will be measured using the Visual Analogue Scale, Cox Retrospective Symptom Scale, diary entries, the Self-rating Depression Scale, and the Self-rating Anxiety Scale. The safety of moxibustion will be assessed at every visit.

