**Table 2 Tab2:** **Study design schedule**

**Period**	**Baseline**	**Inclusion**	**Treatment**			**Follow-up**		
Visit		1	2	3	4	5	6	7
Menstrual cycle	−3 month	0 month	1 month	2 month	3 month	4 month	5 month	6 month
Patients		√						
Inclusion and exclusion criteria		√						
Informed consent		√						
Physical examination		√			√			
Medical history		√						
Comorbidities		√	√	√	√	√	√	√
Outcomes								
CMSS			√	√	√	√	√	√
VAS	√	√	√	√	√	√	√	√
RSS		√						
SDS and SAS		√			√			
Dysmenorrhea diary	√	√	√	√	√	√	√	√
PGF2a, PGE2		√			√			
Gynecological abdominal ultrasound B	√							
Trial evaluation								
Patient’s compliance					√			√
Reasons for dropout or withdrawals					√			√
Adverse events					√			
Safety evaluation								√

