### Interventions

Acupuncturists must receive a license from the Ministry of Health of the People’s Republic of China and take an educational course to ensure their strict adherence to and familiarity with the study before they become eligible to treat patients in this study. Those participants allocated to a treatment group will be requested to attend (with their partner or support person if available) a training course and demonstration session by their tutors. The training course involves advice, demonstration of moxibustion, and instructions on how to do moxibustion safely at home. The woman or her partner or support person will be trained to light the moxibustion sticks and to hold an individual stick 2.5 to 3 cm above the two acupoints (SP6 and CV4). The participants will be told not to make the acupoints uncomfortable during treatment. They will be requested to perform this treatment for five to 10 minutes on each acupoint once a day for five to seven consecutive days, and will be supplied with sufficient moxibustion sticks to do so in each treatment period.

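### The text promises adverse event assessment at every visit, but Table 2 schedules it only at visit 4, with a safety evaluation at visit 7

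*Protocol article*

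**What the plan says.** The Abstract (Methods/Design) states: "The safety of moxibustion will be assessed at every visit". The Safety monitoring section repeats this for adverse events: "All unexpected and unintended responses will be reported as AEs by the researcher at every visit". It extends the rule to events that moxibustion may not have caused. The sentence before it lists what is foreseen: "Possible adverse events (AEs) due to moxibustion include blisters, redness, itching, burns, and respiratory symptoms". The section adds that events are entered in the case report form.

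Table 2 (Study design schedule) has two rows on harms. The row "Adverse events" has one tick, at visit 4, the last treatment cycle. The row "Safety evaluation" has one tick, at visit 7, the last follow-up cycle.

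The Interventions section describes treatment by the woman or a helper, after training that includes "instructions on how to do moxibustion safely at home". Treatment is given "once a day for five to seven consecutive days" in each treatment period, and there are three treatment cycles.

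**The concern.** The text and the schedule give different rules for when harms are asked about. Safety is a stated aim in the Abstract, the Background and the Discussion, so the adverse event count is one of the trial's results.

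Most exposure happens at home, out of sight of staff, and it starts in the first treatment cycle. Under the table, a mild burn or a spell of itching in cycle 1 would first be asked about at visit 4, two visits after it could have been. Minor skin events that have healed by then are easily forgotten. The count would then depend on which part of the document staff followed.

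**Working it through.** No formula or published figure bears on this point. The check is a reading of the text against Table 2, column by column.

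**Columns.** Table 2 has nine: the row label, baseline, visit 1 (inclusion), visits 2 to 4 (treatment) and visits 5 to 7 (follow-up), so 1 + 1 + 1 + 3 + 3 = 9. The post-inclusion visits are 2 to 7, which is six.

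**Ticks at the post-inclusion visits.**

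| Source | V2 | V3 | V4 | V5 | V6 | V7 | Count |
|---|---|---|---|---|---|---|---|
| Abstract and Safety monitoring | yes | yes | yes | yes | yes | yes | 6 of 6 |
| Table 2, adverse events | – | – | yes | – | – | – | 1 of 6 |
| Table 2, safety evaluation | – | – | – | – | – | yes | 1 of 6 |
| Table 2, both rows | – | – | yes | – | – | yes | 2 of 6 |

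The shortfall is 6 − 2 = 4 visits: 2, 3, 5 and 6. Of the three treatment visits, one (visit 4) has an entry.

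**Are the tick positions reliable?** The table was read from PDF, so this needs checking.
- The CMSS row is ticked at visits 2 to 7. This matches the primary outcome section, which uses the scale in all three treatment and all three follow-up cycles.
- The compliance row is ticked at visits 4 and 7, the ends of the two periods.
- The adverse events tick is in the same column as the first compliance tick, and the safety evaluation tick is in the same column as the second.
- The spanning headings for treatment and follow-up appear in the first column of each span (visits 2 and 5). The adverse events tick is in the last treatment column, so a merged cell across the treatment period is unlikely, though it cannot be excluded.

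**How does the table mark per-visit items?** Comorbidities, CMSS, VAS and the diary are each ticked at every one of visits 2 to 7. The table therefore has a clear way to show per-visit collection and does not use it for adverse events.

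**Does another instrument fill the gap?** The diary section lists pain attacks, their duration, associated phenomena and medication. The Follow-up section names the diary, the CMSS and the VAS. Neither names skin or respiratory events.

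**The case against.** The best defence is that the text is explicit in two places and states the fuller rule. In Table 2, adverse events are grouped under trial evaluation with compliance and reasons for dropout, which are ticked only at visits 4 and 7. Reasons for dropout cannot sensibly be gathered only then, so the ticks in this block may mark end-of-period summaries. Staff also see or contact participants at every visit and record comorbidities each time. Finally, the article condenses a fuller protocol, and the case report form may well have an adverse event page for each visit. This lowers the chance that events are missed in practice, but it does not remove the contradiction. The table does not say that its ticks mean summaries.

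A reader might infer several stronger points that the document does not support:

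- **That burns and blisters fall outside the adverse event definition**, because the rule speaks of unexpected and unintended responses. The preceding sentence names them as possible adverse events, and a burn is plainly unintended. The wording is clumsy, but the intent is probably to include them.
- **That safety is entered only once.** This overlooks the tick at visit 7. With both rows the count is 2 of 6.
- **That practice will vary between sites.** The Setting section says the trial is single-centre.
- **That the number of home sessions measures the loss.** With 74 per group, three cycles and five days, the two treatment groups give 2 × 74 × 3 × 5 = 2,220 sessions. With seven days for both groups, as the Interventions section allows, they give 2 × 74 × 3 × 7 = 3,108. With seven days for group A and the five days that the group B section states, they give 74 × 3 × 7 + 74 × 3 × 5 = 2,664. All three totals assume full adherence and no dropout, although 15% dropout is planned for. They describe exposure and say nothing about how many events go unrecorded.

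**Conclusion.** The plan is wrong as written: the text and Table 2 contradict each other on when adverse events are assessed. The gap is four of six post-inclusion visits, including two of the three treatment visits.

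Under-counting of harms is a possible consequence, conditional on staff following the table. The document does not say that they will, and it gives no figure from which a number of missed events could be derived.

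The conclusion rests on the tick positions, which agree with the other rows of the table. The contradiction touches no efficacy endpoint, sample size or significance level, and the text already states the fuller rule. It should be corrected because it bears on a stated aim, but it does not put the trial's main conclusion at risk. The wording of the reporting rule is a secondary matter of clarity.

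**What to change.** 1. In Table 2, tick adverse events at each of visits 2 to 7, for all three groups, so that the schedule matches the text. Asking the waiting list group in the same way keeps the comparison of event rates fair. If the visit 7 safety evaluation is meant as an overall summary, label it so.
2. In Safety monitoring, replace the phrase about unexpected and unintended responses with any untoward event, whether or not expected and whether or not related to moxibustion. The rule then clearly covers the burns, blisters, redness and itching listed just before it.
3. Check the case report form in use, since the Trial status section says recruitment has begun. If it already has an adverse event page at every visit, only the table and the sentence need correcting. If it follows the table, correct the form too and record the date of the change.

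The cost is one table row, one sentence and slightly more data entry. The observed adverse event rate will probably be higher, because events are asked about more often. Treatment is unchanged.

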## Discussion

This proposed trial is a randomized, controlled clinical trial with separation of the practitioner, assessor, and statistician. The aims of this trial are to evaluate the efficacy and safety of moxibustion for treating PD, and to identify the optimal interventional time of moxibustion for PD treatment.

The form of moxibustion used in this trial will be suspended moxibustion treatment. When suspended moxibustion is applied to acupoints, the patient will have non-local or non-superficial heat sensation, such as penetrating heat, expanding heat, and transmitting heat, as *DeQi* appears. Selection of optimal acupoints for PD plays an important role in moxibustion treatment effectiveness. In practice, the treatment effect of moxibustion is affected by many other influential factors, including the intensity of heat stimulation, the ingredients of the moxa pillar, and the moxibustion sensations experienced. The most important factor contributing to the effectiveness of moxibustion is thought to be the selection of proper interventional time. However, in existing studies, interventional timing of moxibustion was not included as a key variant to be assessed.

In another undergoing study, we mainly focused on the effectiveness of moxibustion for pain relief in PD, which can be referred to the published protocol [32]. As to the current one, it is conceived on the basis of the former one. As indicated by the results from the initial analysis, moxibustion is effective for PD pain management; thus we want to further assess the impact of intervention time of moxibustion on the outcome of treating PD, so as the physiological tests’ change by treatment. In clinical practice, moxibustion treatment for PD can also be differed by the intervention timing in China, and there is no relative study on this focus. Thus we carried out the present study as a continuum which is reported by the current protocol. It is anticipated that the result may demonstrate the optimal interventional timing for PD and further extend our understanding of intervention from a chrono-therapeutic perspective, which will be highlights of our further reports. Moreover, the present study that was designed in accordance with the Consolidated Standards of Reporting Trials (CONSORT) statement, and guidelines will provide useful information to guide the clinical practice of moxibustion for PD.

In addition, our study may also have the following strengths which will be potential points of discussion in the final reports. The dysmenorrhea diaries will be used to record the symptoms and management of menstrual pain in every menstrual cycle; these diaries are important for quality monitoring of the recurrence of new PD episodes. Besides the evident physical concerns, PD may be particularly disruptive to adolescent girls and women who experience mood fluctuations, such as depression or anxiety. There is increasing evidence that psychological disorders coexist with dysmenorrhea, and these conditions may synchronize with menstrual pain. The question remains whether anxiety and depression make women prone to suffering from dysmenorrhea, or whether dysmenorrhea causes anxiety and depression. We believe that women with mood changes tend to have lowered pain thresholds compared with mentally healthy women. Anxiety and depression disrupt patients’ experiences, expressions, behaviors, and pain-coping responses. Therefore, a better understanding of the relationship between psychological characteristics and PD is crucial to the assessment of the effectiveness of moxibustion as a treatment for PD. Hence, we will apply the SAS and the SDS to examine the link between PD and psychological symptoms of depression and anxiety among dysmenorrhea sufferers.

On the other hand, there are also limitations to this study. Concealment is the most critical factor in the allocation process, with a high risk of bias possibly generated by unconcealed allocation [33]. One limitation of this study is the possibility of a high risk of bias regarding blinding, as the waiting list group will be used as a control instead of a group receiving a sham procedure. Another limitation is that as moxibustion treatment will begin five to seven days before menstruation or at the onset of pain, the treatment may interfere with the menstrual period; treatment may cause menstruation to occur one or two days sooner or later than the usual cycle. Therefore, it may be difficult to predict an exact menstruation start date for the patients, and this may affect the therapeutic effect.

It is believed that this trial will provide good evidence to demonstrate the efficacy and safety of moxibustion for patients with PD. Moreover, it will be of great significance for clinical practice to identify an optimal moxibustion treatment time for PD.

## Trial status

The trial is currently in the recruitment phase. Participant recruitment started in June 2014, and is expected to end in September 2015.

## Abbreviations

CMSS: Cox Menstrual Symptom Scale
CRF: Case report form
FAS: Full analysis set
IRB: Institutional Review Board
PD: Primary dysmenorrhea
PPS: Per protocol set
RCT: Randomized controlled trial
RSS: Cox Retrospective Symptom Scale
SAS: Self-rating Anxiety Scale
SDS: Self-rating Depression Scale
TCM: Traditional Chinese Medicine
VAS: Visual analogue scale
